**CAMBRA Trial Protocol**

**[name]**

October 2006

1. **TRIAL IDENTIFIER**
   1. **Full title of trial**

Magnet therapy for the relief of pain and inflammation in rheumatoid arthritis: a randomised double-blind placebo-controlled trial.

- 1. **Acronym**

CAMBRA (Copper And Magnetic Bracelets for Rheumatoid Arthritis)

- 1. **Chief investigator**

[name] - Research Fellow

1. **THE NEED FOR A TRIAL**
   1. **What is the problem to be addressed?**

The proposed trial will investigate the therapeutic effectiveness of magnet therapy when used as an adjunct to practitioner led management of pain and inflammation in rheumatoid arthritis (RA). Possible effects on other major health outcomes will also be considered. This will involve a comparison of treatment effects between a commercially available magnetic device and three control devices, which are intended to act as placebos. This addresses a need for rigorous scientific evidence on the subject.

- 1. **What is the principal research question to be addressed?**

The primary objective of this trial is to determine whether or not a widely available permanent static magnetic device (PSMD) provides any true therapeutic benefit for patients with RA in terms of pain and inflammation.

- 1. **What are the secondary research questions to be addressed?**

Secondary objectives of this trial are:

- to determine the actual therapeutic effectiveness of a PSMD in terms of the following additional outcomes:
  - functional status and disease activity
  - general health
  - quality of life
  - use of analgesic medication
- to identify specific factors that may predict actual therapeutic benefit derived from magnet therapy in terms of major outcomes.
- to identify any specific factors which mediate observed placebo effects.
- to report any adverse events or reactions relating to the safe use of devices employed.
- to gather economic data which may be used to evaluate the cost-effectiveness of magnet therapy.
  1. **Why is the trial needed now?**

Rheumatoid arthritis (RA) is a chronic inflammatory autoimmune disease which typically begins to develop between 30 to 50 years of age. It is estimated that 387,000 people in the UK have RA, with three times more women affected than men. RA involves periodic inflammation of the synovium in joints of the hand, wrist, foot, knee or shoulder. This causes swelling of the joint capsule and irritation of nerve endings, producing pain and resulting in damage to both bone and cartilage. In turn this may lead to both disability and mortality (ARC 2002, ARC 2003). Favoured diagnostic criteria are those of the American College of Rheumatology (Arnett et al 1998).

The burden which RA imposes upon both the NHS and the economy in general is considerable. It is reported that over just a one year period (1999 to 2000) inflammatory arthritis accounted for 1.9 million GP consultations, 45,887 hospital admissions and a loss of £833 million in productivity (ARC 2002). For the individual the consequences of RA may be devastating.

Treatment of RA is currently dominated by the use of medication. Non steroidal anti-inflammatory drugs (NSAIDs) are the most widely used pharmacological agents, although 2nd generation anti-inflammatories in the form of Cox-2 inhibitors may be preferable (Madhok et al 2000). Patients with RA are also frequently prescribed disease modifying anti-rheumatic drugs (DMARDs). Whilst recently developed biological agents in the form of TNF-α antagonists have been shown to prevent damage (Emery 2006). Whilst such drugs may alter disease progression, people with arthritis rarely find that they are entirely adequate for the purpose of pain control. Therefore analgesics are also typically prescribed as an adjunct (Jordan et al 2004).

The fact that all commonly prescribed drugs for rheumatoid arthritis are associated with unwanted side effects is worrying for both practitioners and patients. For example, DMARDs are associated with high levels of toxicity and therefore cannot be tolerated for long periods (Emery 2006). Moreover, NSAIDs have been shown to cause gastrointestinal ulcers, which may result in perforation, bleeding and death (Rodriguez and Jick 1994, Madhok et al 2000, Walker-Bone et al 2000).

Over recent years health professionals have witnessed a patient led revolution in the use of complementary and alternative medicine (CAM). Whilst reliable estimates for CAM use are hard to obtain, results of a recent population based survey indicated that around 28% of the UK adult population used some form of CAM in just one year (Thomas et al 2001). However, it has also been shown that people who experience chronic pain are twice as likely to try CAM (Astin 1998). One might therefore anticipate that patients with RA would be included amongst this group. Indeed, this appears consistent with suggestions that almost 60% of people with arthritis use complementary therapy (ARC 2000). In part, such popularity may also be attributed to the perception, albeit sometimes misguided, that complementary therapies lack side effects and therefore represent a safe and ‘natural’ alternative to drugs (Madhok et al 2000, Ernst 2004). Alternatively this may simply relate to a rise in holistic attitudes (Astin 1998, House of Lords 2000).

Whatever the case, such treatments have typically been viewed with scepticism by the medical community. Yet assumptions which directly equate lack of previous scientific evidence to lack of therapeutic efficacy should be challenged. Rather attention should be drawn to the fact that until recently CAM accounted for less than 1% of total research budgets (Wider and Ernst 2003). A figure which is grossly disproportionate to the measurable contribution which CAM makes towards first-contact primary care (Thomas et al 2001). With a growing emphasis on patient choice (NHSE 1998) CAM is now being recognised as a largely untapped resource which offers the potential for therapeutic innovation within the NHS. This view is supported by both the House of Lords and the UK government, which have recommended a major increase in funding for CAM research (House of Lords 2000; Department of Health 2001).

Perhaps one of the most intriguing yet under researched forms of CAM is that of magnet therapy. Quite simply it involves the application of magnetic materials on or very close to the skin over prolonged periods of time. This encompasses a wide range of interventions involving different types of devices, different strength magnetic fields and different modes of administration (Hinman 2002). For example, devices may be unipolar, in which case only one magnetic pole faces towards the skin, or bipolar when two or more magnets are used which face in opposite directions (Trock 2000). However magnet therapy should not be confused with pulsed magnetic field therapy, which involves brief exposure to much stronger electromagnetic fields.

Fascination with the potential health benefits of magnetic forces dates back to antiquity, although in recent times this topic has received a resurgence of public interest (Basford, 2001). Magnet therapy now appears to be one of the most widely used forms of CAM for the management of chronic pain associated with musculoskeletal disorders such as RA, with many patients demonstrating willingness to privately purchase permanent static magnetic devices (PSMDs). Indeed, it is estimated that the worldwide market in PSMDs accounts for somewhere between $2 and $5 US billion (Weintraub 1999, Aspy et al 2002).

Whilst such devices are widely claimed to help alleviate pain for a range of disorders, there appears to be no clearly identified mechanism of action, although theoretically this might involve a reduction in inflammation (Trock 2000). Scientific evidence relating to effectiveness of magnet therapy is however reported to be equivocal (Finegold and Flamm 2006). This has lead to calls for larger and more rigorous randomised controlled trials to determine the actual therapeutic effectiveness, safety and cost-effectiveness of magnet therapy for specific pathological conditions (Ratterman et al 2002; Hinman, 2002).

To the authors’ knowledge only one RCT has yet to focus specifically on the effects of magnet therapy for patients with RA.Segal and colleagues (2001) randomly allocated 64 patients with RA of knee to wear either a bipolar magnetic device (MagnaBlocTM) or a seemingly identical unipolar device. The experimental device consisted of four magnets disks (each 190mT) whereas the control device included just one magnetic disk (72mT) and three non-magnetic disks. Devices were attached to the knee for a period of one week in both the treatment (n= 38) and control (n = 26) groups. Both participants and researchers were reportedly blind to treatment allocation. Although participants allocated to the MagnaBlocTM group demonstrated a statistically greater reduction in pain throughout the intervention phase than those in the control group, the study failed to demonstrate a statistically significant difference in pain between the two groups at the end of the 1 week period (p = 0.23). In terms of surrogate measures of inflammation (C-reactive protein and erythrocyte sedimentation rate) no difference was observed between treatment and control groups. In the absence of any evaluation of success in blinding, it is interesting to note participants global assessment of disease activity improved to a significantly greater extent in the treatment group than in the control group (p < 0.01).

Whilst results presented by Segal and colleagues may be challenged on the basis of poor trial design and lack of statistical power, this study nevertheless highlights a number of other methodological weaknesses which characterise other published trials of magnet therapy. Importantly, medication use was not measured although participants were likely to alter their use of analgesics as a response to changes in pain intensity. Any true benefit derived from magnet therapy may therefore have been masked by a reduction in medication use. Trials of magnet therapy should also give participants the opportunity to use devices in a manner which reflects common practice within the real world. Since magnet therapy is generally understood to involve prolonged periods of exposure to magnetic fields, it may be argued that short periods of exposure will prove insufficient for any cumulative therapeutic effect to occur. In the case of the trial described above, an exposure period of one week may well have been inadequate. Certainly compliance should also have been reported since there is no guarantee that trial participants actually wore the devices as recommended. Even if analysis of data is by intention to treat rather than by active treatment, this information will still be of value.

Perhaps the greatest methodological challenge faced by trial of magnet therapy however is that of providing adequate control devices against which any ‘true’ effects from magnet therapy may be assessed. RCTs which incorporate a placebo control group are generally perceived as methodologically superior to those which do not. This is especially the case for trials involving new treatments and subjective outcome measures (Avenell et al 2004, Fergusson et al 2004). The key methodological advantage of placebo controlled trials over open trial designs relates to the ability to blind participants, clinicians and researchers to the allocation of experimental and control treatments (Vickers and de Craen 2000). This helps to avoid systematic bias resulting from differences in the perceived or desired effectiveness of treatments which may alter the outcomes being assessed (Schulz and Grimes 2002, Campbell 2003, Akobeng 2005).

For trials of magnet therapy successful blinding is hampered by the fact that magnetism is a necessary quality of experimental devices which can in most cases be detected with relative ease. Trials which report superior patient outcomes for a magnetic device as opposed to a non-magnetic control device are therefore likely to be criticised on the basis that results may be attributable to non-specific (placebo) effects (Pope and McNally 2002, Patterson and Dieppe 2005). This highlights the need to evaluate success of blinding (Fergusson et al 2004).

The problem of blinding is not necessarily without solution however. One approach is to use an attenuated control device, which retains a weak magnetic force and therefore helps to prevent participants and researchers from correctly identifying the device as a placebo or sham (e.g. Segal et al 2001, Harlow et al 2004). The obvious limitation of this approach however is that rather than being completely inert the control device may have some therapeutic action. As such, this may produce a more conservative estimate of treatment effect between groups. An alternative approach, yet to be reported, is to use a non-magnetic comparator which is marketed commercially as having similar therapeutic benefits, but which in actual fact is ineffective. Such a device would need to have face validity and be used in a similar fashion to the experimental magnetic device. In this sense copper bracelets may be ideal.

Whilst research findings point towards serum copper imbalances in patients with arthritis (Grennan et al 1980, Youssef et al 1983, Milanino et al 1993) it is likely that this reflects a natural metabolic response, rather than a cause, of inflammation (Weber 1984). The link between dermal copper absorption and pain relief in arthritis may therefore be rather tenuous. However, given the popular use of copper bracelets it is therefore surprising that no rigorous scientific research appears to have been conducted on the therapeutic effectiveness of such devices.

In the most widely cited study on this topic Walker and Keats (1976) randomised 240 arthritis sufferers into three groups (see also Walker et al 1981). Group 1 wore a copper bracelet for one month and then an aluminium bracelet for a further month. Group 2 wore identical devices but in reverse order and Group 3 wore no device. From this Walker and Keats reported that significantly more participants rated the copper bracelet as superior than the aluminium bracelet and that copper bracelets actually lost weight by an average of 13mg/month. This appears to support the theory that copper may be leached into the skin and that this may have had a positive therapeutic effect on arthritis symptoms. However, Walker and Keats failed to demonstrate any positive correlation between the weight loss of individual bracelets and perceived efficacy. Major criticisms of this study centre on selection bias and measurement error. For example, 163 or 68% of all participants were excluded from the analysis. Some of whom were removed due to poor compliance, whilst others were excluded on the grounds that their bracelets actually gained weight. Certainly the finding that bracelets included in the analysis lost weight is not therefore surprising. Furthermore, blinding is likely to have been compromised since the control bracelet would have appeared different in weight, colour and corrosion. Indeed, such findings have yet to be replicated elsewhere.

Seemingly contradictory evidence rejecting a link between dermal copper absorption and pain relief in arthritis comes from Shackel and colleagues (1997). This involved a randomised double-blind trial of copper-salicylate versus placebo gel for pain relief amongst 116 participants with osteoarthritis. Whilst one would expect copper to be absorbed more readily in a gel preparation than would be the case with a copper bracelet, findings from this trial failed to demonstrate any difference between the copper-salicylate gel and the placebo gel in terms of pain relief, ratings of treatment efficacy or use of medication after 1 month of treatment. Whether these findings could be generalised to patients with RA is however open to question.

Overall, it has been shown that RA is a common inflammatory musculoskeletal disease which represents a significant burden to the UK health system and the economy. For the individual its effects are both distressing and disabling. Conventional drug treatments for RA may fail to control pain and present a risk to the individual. Increasingly therefore patients with arthritis may be turning to complementary and alternative therapeutic approaches to pain management, such as magnet therapy. However historical underinvestment in CAM research has resulted in a lack of scientific evidence concerning the therapeutic effectiveness of such devices. Further pragmatic research within this field may therefore lead to innovative therapeutic advances in the cost-effective management of diseases such as RA. Within this context the proposed trial will seek to offer a meaningful scientific evaluation of the true therapeutic value of magnet therapy for RA using a novel methodological approach to overcome some of the inherent challenges encountered by research in this field.

- 1. **Systematic reviews**

A review of scientific databases (Cochrane Library, Medline, AMED and CINAHL) confirms an overall paucity of rigorous scientific research into the therapeutic effectiveness of magnet therapy for RA, or indeed any other condition. As such, this search failed to reveal any systematic reviews on the topic, although a number of ‘critical’ reviews were identified.

Hinman (2002) reviewed findings from 14 RCTs and repeated measures design studies involving magnet therapy and pain as an outcome in humans. Of these, 6 demonstrated a statistically significant reduction in pain following magnet therapy, with a further 3 studies showing a non-significant reduction in favour of magnet therapy. More recently, Eccles (2005) reported a review of 21 RCTs, 13 of which demonstrated statistically significant analgesic effects associated with magnet therapy. This review also showed a tendency for higher quality trials to show positive effects. Inconsistencies in findings between trials may be attributed to a variety of factors including variability in methodological quality, differences between device investigated and clinical heterogeneity between conditions studied.

As part of an allied research programme a systematic review of magnet therapy for chronic pain is planned. This will be of direct relevance to the proposed trial.

- 1. **Other relevant trials currently being undertaken**

A search of The Cochrane Central Register of Controlled Trials (CENTRAL) and the *meta*Register of Controlled Trials (*m*RCT) revealed no RCTs of magnet therapy for arthritis currently in progress, apart from that of the MACROPOD trial.

MACROPOD (ISRCTN 18518978) is a randomised double-blind placebo controlled crossover trial of magnet therapy for pain relief in osteoarthritis, which is currently at the analysis stage. In total 45 participants were randomly allocated to one of four treatment sequences consisting of four phases, with each phase lasting one month. Participants each wore a MagnaMaxTM bipolar bracelet (mean strength 200.9mT, SD 17.7), an attenuated MagnaMaxTM (45.3mT, SD 12.0), a non-magnetic MagnaMaxTM and a copper bracelet. Outcomes measures included a 10cm pain visual analogue scale, WOMAC, McGill Pain Questionnaire, SF-36, EQ-5D together with economic items. Medication use was measured by triangulation of diary records, prescription records and by manually counting remaining tablets and capsules before and after each phase. Whilst originally developed as a pilot study for future trials of magnet therapy, MACROPOD is nevertheless fully powered for the purpose of demonstrating a meaningful clinical difference between the commercially available PSMD employed and the three ‘placebo’ devices in terms of the primary outcome. Findings from this study are due to be published towards the end of 2006.

- 1. **How will the results of the trial be used?**

Further research on this topic would seem wise given that conclusive findings either way was would prove beneficial. If effectiveness can be demonstrated then magnet therapy may become a valuable addition to clinical practice, improving quality of life amongst patients and lowering demand for both consultations and specialist referrals. Moreover, it may serve to reduce reliance on potentially harmful drug treatments, thereby preventing unnecessary adverse events. In economic terms it is also worthwhile noting that one-off costs of providing magnetic devices are likely to be far lower than those of repeatedly prescribing analgesic medication. Therefore if, for example, drug prescription costs for arthritis and related conditions could be reduced by just 1% then this would result in an annual saving to the NHS of roughly £3.4 million per annum (ARC 2002). Conversely, if this trial demonstrates that magnet therapy is ineffective then this may serve to educate patients and prevent unnecessary private expenditure. Perhaps more importantly however the present study addresses an immediate need for guidance which will benefit health care professionals and assist in making appropriate health policy decisions.

1. **THE PROPOSED TRIAL**
   1. **What is the proposed trial design?**

The trial will employ a randomised crossover design. Therefore each participant will act as his or her own control. The principle advantage of a crossover design is that error variance is reduced, thereby minimising the sample size required. Crossover designs are also extremely well suited to exploratory research of new treatments (Senn 2002).

- 1. **What are the planned trial interventions?**

Given the inherent difficulties in developing a ‘perfect’ placebo for magnet therapy, this study will build upon methodology employed within the MACROPOD trial by incorporating three distinct control devices. This represents a comprehensive and concerted attempt to overcome different limitations associated with each individual device in terms of blinding and potential therapeutic action. All participants will therefore undergo four treatment phases each lasting for a period of five weeks:

**Phase A: Full strength MagnaMaxTM (experimental device)**

The device worn during this phase will be a commercially available bipolar magnetic wrist strap which is marketed for the purpose of relieving pain in conditions such as rheumatoid arthritis. A number of manufacturers have been approached, one of which has agreed to supply their device (MagnaMaxTM) at a discounted rate. Magnetic strength will be checked using a calibrated Hall effect probe prior to distribution. However this device was also used in the MACROPOD trial, and is known to have maximum surface field strength of between 180-220mTesla which is common for devices of this type.

**Phase B: Attenuated MagnaMaxTM (placebo)**

This device will be identical to the experimental device with the exception that the magnetic field strength will be reduced to between 25 to 35 mT. This will be confirmed using a Hall effect probe. Participants are unlikely to identify this as a placebo, although it is possible that the weak magnetic field produced may have some therapeutic effect.

**Phase C: Demagnetised MagnaMaxTM (dummy)**

This device will appear identical to the experimental device, although it will have no magnetic properties. This device should therefore be entirely inert. Participants are likely to realised that device has been demagnetised and therefore view it as a placebo.

**Phase D: Copper bracelet (placebo)**

Participants will also test a commercially available copper bracelet. As copper bracelets are widely used for pain relief by the general public it is likely that participants may expect this to have some therapeutic benefit. Whether or not this device actually represents a valid placebo is a question which will be addressed as part of the trial.

Participants will be asked to wear each of these devices for a minimum of 12 hours per day, although ideally they should be worn continuously.

- 1. **What are the proposed practical arrangements for allocating participants to the trial groups?**

Participants will randomly allocated to 1 of 24 possible treatment sequences. Treatment sequences will consist of four phases, with each phase corresponding to a particular device (as shown in Appendix 1). This method is preferred over the use of a Latin square design, as this will help to minimise possible analytical bias associated with attrition.

Randomisation will be performed remotely and independently by the York Trials Unit using a relevant computer programme to avoid any bias in sequence allocation. Block randomisation will be unnecessary. The randomisation code will be will be concealed from the chief investigator until all data collection has been completed. Once the full randomisation sequence for all potential participants has been determined, then devices will be packed and sealed in identical padded boxes, distinguishable only by a trial ID number and order in which they are to be distributed.

- 1. **What are the proposed methods for protecting against other sources of bias?**

Several additional methods will be employed to counter potential threats from bias in terms of both the internal and external validity.

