**Pill Count**

Participants will be visited at home by the chief investigator at recruitment and at the end of each treatment phase. With the participants help and prior consent (obtained at recruitment) a ‘pill count’ will then be conducted. This will involve counting the remaining number of tablets or capsules that the participant has in their possession for each analgesic, NSAID or DMARD received on repeat prescription. Issue dates will also be recorded. At a later stage prescription records will be obtained from each participant’s general practice. Together this information will be used to estimate use of prescription medication during each treatment phase. This approach has been used successfully by both the RESPECT trial (Wong et al 2004) and the MACROPOD trial. Before this, participants will also be asked to estimate the extent to which their medication use altered during each phase, using a 5-point Likert scale. This questionnaire item will be used for the purpose of validating estimated medication use.

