Each focus group will be provided with a detailed outline for the proposed trial, together with trial materials in advance. Feedback will be sought on a variety of issues, including possible weaknesses with trial methodology and suitability of written material. The groups will help to identify any special considerations associated with the study of rheumatoid arthritis which may have been overlooked. Each group will also discuss issues specific to the use of blood tests, such as their acceptability to study volunteers. Information gathered will be used to refine the trial protocol. This may result in an application for the approval of minor amendments from local research ethics committee concerned.

1. **DETAILS OF THE TRIAL TEAM**
   1. **Trial management**

The Department of Health Sciences at The University of York will act as the co-ordinating centre for CAMBRA. This trial will be led by [name] as the chief investigator, who will be responsible for clinical and scientific co-ordination, together with day to day management. This will include recruitment of all general practices and participants, data collection, analysis and dissemination of findings. [name], as Director of the York Trials Unit will be responsible for supervising patient randomisation and data management. He will also act as an advisor on matters relating to trial design and methodology. [name] will act advisor on matters concerning the use and evaluation of complementary and alternative medicine. [name] will serve as a statistical advisor to the trial. [name] from The University of Hull will advise on matter concerning general medical practice. As a co-investigator for MACROPOD, he will also contribute towards the evaluation of this trial. For the purpose of trial development further support will be sought from a leading rheumatologist.

- 1. **Participating centres**

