Either nine or twelve general practices will be recruited across three PCT regions. Practice managers / practice staff will identify potentially eligible patients from medical records with support from the chief investigator. Honorary contracts will be obtained for the chief investigator for each of the PCTs involved. Administrative staff from each practice will then contact patients by post. Each patient will be sent an information sheet, letter of invite to participate and a standard covering letter expressing support for the trial, signed by one of the GPs. Patients will be asked to contact the chief investigator if they are interested in participation.

General practice will be informed when a patient is recruited into the trial. A series of four appointments will then be made for blood samples to be taken from the participant by either a nurse or a phlebotomist located within the practice. Administrative staff will be responsible for organising these appointments, sending samples for analysis and providing the trial with the results. Following all other data collection activities, each practice will be visited by the chief investigator during which prescription histories and blood tests results will be obtained.

1. **APPENDICES**
   1. **Appendix 1: Randomisation sequence for device allocation**

|  | | **Order of treatment phases (weeks)** | | | | | | | |
| --- | --- | --- | --- | --- | --- | --- | --- | --- | --- |
| **wk1** | **weeks**  **1 to 5** | **wk6** | **weeks**  **7 to 11** | **wk12** | **weeks**  **13 to 17** | **wk**  **18** | **weeks**  **19 to 23** |
| **Sequence Number** | **1** | Recruitment | *Full Strength* | wash out | *Attenuated* | wash out | *Demagnetised* | wash out | *Copper* |
| **2** | *Full Strength* | *Attenuated* | *Copper* | *Demagnetised* |
| **3** | *Full Strength* | *Demagnetised* | *Attenuated* | *Copper* |
| **4** | *Full Strength* | *Demagnetised* | *Copper* | *Attenuated* |
| **5** | *Full Strength* | *Copper* | *Attenuated* | *Demagnetised* |
| **6** | *Full Strength* | *Copper* | *Demagnetised* | *Attenuated* |
| **7** | *Attenuated* | *Full Strength* | *Demagnetised* | *Copper* |
| **8** | *Attenuated* | *Full Strength* | *Copper* | *Demagnetised* |
| **9** | *Attenuated* | *Demagnetised* | *Full Strength* | *Copper* |
| **10** | *Attenuated* | *Demagnetised* | *Copper* | *Full strength* |
| **11** | *Attenuated* | *Copper* | *Full Strength* | *Demagnetised* |

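### The code may be released to the chief investigator once data collection ends, before per-phase medication use has to be derived, so the protocol permits that derivation to be done unblinded

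*Protocol*

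**What the plan says.** The release rule is in the section on practical arrangements for allocating participants. The code is to stay "concealed from the chief investigator until all data collection has been completed". Derivation of outcomes, data cleaning and database lock are not mentioned as conditions.

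The Pill Count section describes how medication use is obtained. "Participants will be visited at home by the chief investigator at recruitment and at the end of each treatment phase", and at these visits the remaining tablets or capsules of each repeat-prescription analgesic, NSAID and DMARD are counted and issue dates noted. "At a later stage prescription records will be obtained" from the general practices, and then: "Together this information will be used to estimate use of prescription medication during each treatment phase".

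The Participating centres section says when those records come in: "Following all other data collection activities, each practice will be visited by the chief investigator during which prescription histories and blood tests results" are obtained.

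The Trial management section sets out the chief investigator's duties: "This will include recruitment of all general practices and participants, data collection, analysis and dissemination of findings". It makes the Trials Unit director responsible for supervising randomisation and data management.

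Use of analgesic medication is listed among the secondary research questions. The planned-analyses section also uses medication, together with compliance, to adjust the estimated device effects in a secondary step.

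**The concern.** The title calls the trial double-blind, and the protocol takes care to keep the researcher blind during follow-up, with sealed identical boxes, inspection of the returned seals and a written request that participants do not describe their devices. The release rule lets that protection end as soon as the last record is in hand.

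For most outcomes this is harmless, because the value is fixed when it is recorded. Medication use is different: it is constructed from several sources after they have been assembled. In a four-period crossover, anyone holding the code knows which device each participant wore in each phase. An error of apportioning made without that knowledge adds noise but has no reason to favour a device. A discretionary decision made with it can differ by device. At stake are the medication-use comparison and, through the covariate, the medication-adjusted device effects. The protocol itself gives this variable weight: it faults an earlier magnet trial in rheumatoid arthritis for not measuring medication use, on the ground that a change in use could mask a benefit.

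**Working it through.** The protocol gives no figure to reproduce. The check is one of order and responsibility, with a short count to show where judgement enters.

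**Order of events**

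1. At recruitment and at the end of each phase the chief investigator visits, and pills are counted. The code is concealed (Pill Count; allocation section).
2. After all other data collection, the chief investigator visits the practices and obtains prescription histories and blood results (Participating centres). This visit is itself data collection, so the code is still concealed.
3. Data collection is now complete, and the condition for concealment has lapsed (allocation section).
4. Counts, issue dates and prescription histories are combined into medication use per phase (Pill Count). This needs the input from step 2, so it cannot be completed before step 3. No blinding is stated for it.
5. Analysis follows, under the chief investigator's responsibility (Trial management).

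Nothing in the protocol requires step 4 to be finished before the code is released.

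**Whether step 4 involves judgement**

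Inputs: four phases of 5 weeks, three wash-out weeks between them, a visit at recruitment and one at the end of each phase (sections on treatment duration and follow-up; Appendix 1).

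- Phase 1: from recruitment to the end of week 5 is 5 weeks, all with a device.
- Phases 2 to 4: end of week 5 to end of week 11, 11 to 17, and 17 to 23. Each interval is 6 weeks = 1 wash-out week + 5 device weeks.
- Check: 5 + 6 + 6 + 6 = 23 weeks, the stated total.

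For three of the four phases, then, the count covers a period one sixth of which (1/6 = 17%) is not the treatment phase. With complete data from 62 participants, 62 × 3 = 186 of 62 × 4 = 248 participant-phases are in this position. With all 69 recruited it is 69 × 3 = 207 of 69 × 4 = 276. Use over each such interval has to be divided between wash-out and phase, for each drug counted, and the protocol gives no rule for doing so.

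These counts show how often an apportioning decision arises. They do not measure bias: a fixed pro-rata rule applied to everyone would handle the wash-out week without discretion, whether or not the code were known.

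**What is outside the gap**

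- Pill counts, issue dates and prescription histories are all collected before the earliest release.
- The pain VAS, the critical test in the primary analysis, is completed by participants in questionnaires.
- Blood results come from NHS laboratories.

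**The case against.** The strongest reply is that the release rule sets only an earliest time. It does not schedule a release at that moment, and it does not say that medication use will be worked out afterwards. Nor does the protocol say that the estimate is made by hand or by the chief investigator. The Trials Unit director supervises data management, and derivation could well fall under that. All source data are gathered blind. Participants also rate the change in their medication use on a five-point item before each pill count, as a check on the estimates. Derivation rules and the timing of database lock are often set out in an analysis plan or data-management plan, which is not at hand.

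Much of this stands, and it limits the point. A reader might infer that the chief investigator will reconcile the records by hand after unblinding, or that the trial is not blinded for medication use. The protocol supports neither: it leaves open who does the work and when, and only the combination of records already fixed is exposed. A reader might also extend the concern to the pooled disease-activity index, but the protocol identifies no judgement step there that knowledge of the code could influence.

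The reply does not remove the gap. The release trigger is not a detail left for another document; the protocol states it, and sets it at a point that does not cover this derivation. Supervision of data management by the Trials Unit does not require derivation before release. The five-point item is a coarse check and does not fix the derived values. Refinement of the analysis plan towards the end of data collection would help only if it included a derivation rule, which the protocol does not say.

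**Conclusion.** The point holds as a weakness in a stated rule. As written, the protocol permits per-phase medication use to be derived with the code known, possibly by the investigator responsible for data collection and analysis. The conclusion rests on three things the protocol does state: concealment is guaranteed only to the end of data collection, the last input arrives at that end, and three of the four count intervals include a wash-out week with no rule for apportioning it.

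The reach is limited to one secondary outcome and to the medication-adjusted effects in the secondary analysis step. The unadjusted pain VAS and the laboratory markers are not affected.

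No numerical size of bias can be given. A reader might be tempted to multiply a share of phases needing judgement by a shift per judgement, but the protocol supplies neither quantity, nor any ground for assuming that all decisions would move the same way by device. The change is worth making because it is cheap and because blinding of this step cannot be restored once the code has been seen.

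**What to change.** In the section on allocating participants, replace the end of data collection as the release point. Suggested wording: the York Trials Unit will hold the randomisation code, and will not release it to the chief investigator, until medication use in each phase has been derived for all participants and the database has been cleaned and locked. Add that the derivation is to be made from phase number (1 to 4) only, without reference to device.

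The Trials Unit already carries out the randomisation and packs the devices, so no visits, participants or data are added. The cost is a short delay between the last practice visit and unblinding.
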